### Strategies for Improving the Fidelity of Care Providers and Adherence of Participants

The Ayurvedic intervention is standardized and will be administered uniformly as per the protocol. Participants will be screened for suitability before Panchakarma therapy, and the intervention will be withheld in cases of intolerance, fever, respiratory infection, or any other clinical contraindication. To ensure uniformity, all procedures will follow standard operating protocols, and participants will receive patient information leaflets detailing the interventions.

As panchakarma therapies are delivered in an inpatient or closely supervised setting by trained professionals, adherence will be monitored daily through direct supervision and treatment logs. Participants are required to maintain a compliance form to record the intake of both standard care and add-on oral Ayurvedic medications, which will be reviewed by the study team during follow-up visits. Furthermore, to promote participant retention and minimize missing data, follow-up will be reinforced through periodic telephonic contact between scheduled visits.

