Safety assessments will include monitoring for treatment-emergent adverse events throughout the study period. Liver function tests, renal function tests, and complete blood count will be performed at baseline and at the end of the study (day 180) to detect any potential systemic adverse effects. For participants undergoing Basti therapy, adverse events (AEs) will be monitored during the in-patient care.

Participants in the TAU arm will continue with their dopaminergic medications. At baseline, stabilized or optimized dopaminergic doses will be recorded, and any subsequent changes during the trial will be documented along with dates and reasons. Levodopa equivalent daily dose (LEDD) will be calculated at each visit (baseline and follow-ups) using standardized conversion factors and tracked longitudinally.

All clinical and neurophysiological outcome assessments will be performed by a trained SRF with an MD (Ayurveda) qualification, and the routine assessments will be done by the neurologists involved in the study before prescribing the study TAU interventions or deciding changes in interventions. The SRF underwent a 3-month structured training program under the supervision of a neurologist and neurophysiologist to ensure competency in administering both clinical and neurophysiological assessments. The same SRF will also be responsible for data collection throughout the study to maintain consistency.

All outcome measures are evaluated using validated clinical scales and standardized laboratory instruments, as detailed in the manuscript, each with established reliability and validity. Before the commencement of data collection, all laboratory instruments and procedures will be calibrated and standardized. To promote data quality, assessors received formal training, and interrater reliability for the primary outcome measure (MDS-UPDRS Part III) will be established in at least 20% of participants.

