#### Consent

Informed consent will be obtained by the SRF possessing an MD (Ayurveda) qualification, who has been trained in GCP [14] and institutional ethical guidelines for human research. The SRF has prior experience in conducting clinical studies and in obtaining informed consent in accordance with ethical standards.

The consent process will be conducted in the participant’s preferred language, ensuring adequate explanation of study objectives, procedures, potential risks, and benefits. Ample time will be provided for participants to ask questions and decide about participation voluntarily. The entire process will be documented, and a copy of the signed consent form will be provided to each participant.

Any AEs occurring during the course of the trial will be promptly reported to the Data and Safety Monitoring Board (DSMB) as per the approved protocol. Participants experiencing an AE will receive appropriate and immediate clinical care. Each event will be independently reviewed by a committee comprising experts from both the Ayurveda system of medicine and modern medical sciences.

If, upon thorough evaluation, the AE is determined to be related to the investigational intervention, compensation will be provided to the participant in accordance with regulatory requirements through the study’s approved insurance coverage.

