### Harms: AE Collection, Assessment, Reporting, and Management

Participants will be assessed for AEs at each scheduled follow-up visit (days 60, 120, and 180) and during routine hospital visits. Each reported AE will be documented and categorized based on severity, relatedness to the intervention, and expectedness, following standardized guidelines. Laboratory safety assessments, including liver function tests, RFTs, and complete blood count, will be performed at baseline and at the final study visit (day 180) to monitor any potential systemic effects. All recorded AEs will be reviewed by the DSMB, which will assess their clinical significance and provide recommendations for participant safety. SAEs will be promptly reported to the NIMHANS Human Ethics Committee and the sponsor, CCRAS, in accordance with regulatory guidelines.

For participants who discontinue or deviate from the intervention protocol, no further outcome assessments will be conducted, as the primary outcome (MDS-UPDRS Part III) requires evaluation in both ON and OFF medication states, and other assessments (TMS, pulmonary function tests, Montreal Cognitive Assessment, 6-m walk test, and Balance Error Scoring System) are performed in the OFF state. The reasons for nonadherence (eg, adverse effects, lack of perceived benefit, or personal constraints) and nonretention (eg, withdrawal or loss to follow-up) will be systematically documented either during the next scheduled visit or through telephonic communication. These details will be recorded in the case report forms to enable transparent reporting and analysis of participant flow and data completeness.

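### The only dated adverse-event enquiries shared by both arms are 60 days apart, and the calls planned between visits are not stated to ask about events

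*Protocol article*

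**What the plan says.** The protocol article makes two general commitments on harms. Outcome Measures states: "Safety assessments will include monitoring for treatment-emergent adverse events throughout the study period". The Consent section adds: "Any AEs occurring during the course of the trial will be promptly reported to the Data and Safety Monitoring Board".

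The working rule is in the section on AE collection: "Participants will be assessed for AEs at each scheduled follow-up visit (days 60, 120, and 180) and during routine hospital visits". The frequency of routine hospital visits is not given. Outcome Measures adds one further source, in the Ayurveda arm only: "For participants undergoing Basti therapy, adverse events (AEs) will be monitored during the in-patient care".

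The section on fidelity and adherence plans calls between visits: "follow-up will be reinforced through periodic telephonic contact between scheduled visits". Their stated purpose is "to promote participant retention and minimize missing data". Neither their frequency nor their content is described. The compliance form in the same section records intake of medicines and is reviewed at follow-up visits.

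Table 2 has rows for concomitant and rescue medication but none for AEs.

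**The concern.** The commitments cover the whole 180 days, but the dated enquiries are three, and the longest phase of the intervention contains none before the visit that closes it. An event that starts and resolves between visits reaches the record in one of three ways: the participant reports it unprompted, a routine visit happens to pick it up, or it is remembered at the next follow-up. Mild and short-lived events are the ones most easily lost or misdated.

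This matters for three reasons. Safety is part of the trial's hypothesis. AEs are to be summarised by treatment group, so missed events make an arm look safer than it is, and extra monitoring in one arm only makes the two columns harder to compare. The safety board can act only on what has reached the team. Discontinuation is also not rare: the Results section reports 14 of 58 enrolled participants (14/58 = 24%), with reasons not given.

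**Working it through.** The plan states no figure for this, so the check is arithmetic on the schedule and a comparison of the sections.

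**Inputs.** AE enquiry on days 60, 120 and 180 (harms section). Three cycles of 60 days, each with a 5-day preparatory phase and a 47-day oral phase (Group B intervention). The Basti course has 1 + 3 + 3 + 1 = 8 administrations (same section).

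**Gap common to both arms.** 60 − 0 = 120 − 60 = 180 − 120 = 60 days.

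**Make-up of a cycle in the Ayurveda arm.** 60 − 5 − 47 = 8 days remain, which matches the 8 Bastis. Assumptions: one Basti a day, all under in-patient AE monitoring, phases in sequence, and the follow-up visit at the end of the cycle. Then:

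| Phase | Days in 180 | Share | Planned AE contact |
|---|---|---|---|
| Preparatory | 3 × 5 = 15 | 8% | none stated |
| Basti | 3 × 8 = 24 | 13% | in-patient monitoring |
| Oral | 3 × 47 = 141 | 78% | none until the closing visit |

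**Wait to the next scheduled enquiry.** If onset is uniform over a window of L days, the mean wait is L/2 and the maximum is L.
- Treatment as usual: L = 60, mean 60/2 = 30 days, maximum 60.
- Ayurveda arm, oral phase: L = 47, mean 47/2 = 23.5 days, maximum 47.

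The first figure describes a whole interval and the second only the oral phase, so they are not a like-for-like comparison of arms. Both are upper bounds on delay in practice, because routine visits and spontaneous reports are not counted.

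**Effect of one enquiry midway between visits (illustration).** With a call on day 30 of each interval:
- Treatment as usual: two windows of 30 days, mean 15 days, maximum 30.
- Oral phase, starting after day 13: windows of 30 − 13 = 17 days and 60 − 30 = 30 days. Mean = (17 × 8.5 + 30 × 15)/47 = 594.5/47 = 12.6 days, maximum 30.

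**The telephone route.** The article mentions telephone contact twice. The between-visit calls serve retention and completeness. Separately, for participants who stop or deviate, the harms section lets the reasons, adverse effects among them, be recorded "either during the next scheduled visit or through telephonic communication". So even an adverse effect that led someone to stop may wait for the next visit under the rule as written.

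**The case against.** Much can be said for the plan. It would be wrong to infer that AEs are sought only every 60 days: routine hospital visits count, and Basti is monitored in every cycle. It would also be wrong to infer that the calls exclude AEs. The article is silent on their content, it condenses a fuller protocol that may hold the call script, and it already accepts adverse effects by telephone as a reason for non-adherence. Participants may report events unprompted. Dated records of dopaminergic dose changes, together with the concomitant and rescue medication entries, can help recall at visits. The trial is exploratory, with 80 participants and a descriptive safety analysis, and a 60-day interval is not an error in itself.

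All of that stands, and it limits the point to a design weakness. It does not remove it. The article does state a collection rule with named days and does state what the calls are for, so this goes beyond detail left to another document. The supplementary sources are either of unknown frequency, dependent on the participant, or confined to one arm and about 13% of its days.

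The objection on cost is partly right. Call frequency is unstated, so fixed time points are a new commitment. The senior research fellow who performs the blinded assessments also collects data throughout, so another team member has to ask.

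**Conclusion.** The point holds as a modest but worthwhile improvement. Dated AE enquiry common to both arms occurs every 60 days, none is scheduled during the oral phase, and the calls that could fill the gap are not stated to do so. The size is a mean wait of 30 days (maximum 60) under treatment as usual and 23.5 days (maximum 47) in the oral phase. It rests on uniform onset, on Basti filling the 8 unassigned days of each cycle, and on no credit for routine visits or self-report.

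Two stronger readings are not supported. One is that the plan contradicts its promise of prompt reporting: promptness can run from when the team learns of an event, and visits through day 180 do span the study period. The other is that a given share of events will be missed: the documents contain nothing on recall or event rates from which such a share could be computed.

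**What to change.** In the fidelity and adherence section and the harms section, state that the planned between-visit calls include a short scripted AE question, put in the same words and at the same time points in both arms, for example midway between visits. Name an existing team member other than the blinded assessor to ask it, since talk of AEs can reveal allocation. Record answers on the AE form with onset date, and let reporting to the safety board start from the call. Add an AE row to Table 2. Summarise AEs from these common contacts by arm, so that events found only through in-patient Basti monitoring can be told apart.

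If the calls already ask about AEs, a sentence in each of the two sections and the table row are enough.

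The cost is a few minutes per call, a fixed call timetable, a caller who is not the assessor, and somewhat more mild events on record. No treatment changes. At the August 2025 count, 11 participants were continuing and 80 − 58 = 22 places were still to be filled, so up to 33 participants could have been covered from that point.

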### Hypothesis

This study hypothesizes that Ayurveda treatment, when integrated with standard TAU, will be safe and effective in improving clinical and cognitive outcomes in patients with idiopathic PD. It is expected that these therapies will enhance the optimal response to levodopa, potentially leading to better symptomatic control. Ayurveda interventions are hypothesized to modulate cortical excitability measures, which will correlate with improvements in both clinical and cognitive parameters. Furthermore, it is postulated that add-on Ayurveda therapies may induce a significant shift in the Th1/Th2/Th17/T regulatory cell population, along with alterations in plasma levels of pro-inflammatory cytokines and telomere length, which will further correlate with clinical, cognitive, and neurophysiological outcomes. Finally, it is anticipated that autonomic dysfunction, as measured through heart rate variability (HRV), will show significant improvement following Ayurveda interventions, aligning with overall clinical benefits observed in patients with PD.

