### Intervention

The interventions used in this study consist of two arms: group A (control group) receiving conventional TAU and group B (intervention group) receiving add-on Ayurveda therapy along with TAU of PD, prescribed by the treating neurologist.

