### Statistical Analysis

All analyses will be performed using SPSS software. The primary outcome, change in MDS-UPDRS Part III score from baseline to 24 weeks, will be analyzed using a mixed model for repeated measures with treatment, time, and treatment×time interaction as fixed effects and baseline values as covariates. LEDD will be included as a time-varying covariate to account for dopaminergic medication effects. Results will be reported as least-square mean differences with 95% CIs. The main analysis will follow a modified intention-to-treat approach including all randomized participants who receive at least one dose of the assigned intervention, whereas a per-protocol analysis will be performed as a sensitivity check on participants who complete ≥80% of scheduled therapies and medication adherence.

Missing data will be handled under the assumption of data missing at random using the mixed model for repeated measures model, which uses all available data without imputation. Additional sensitivity analyses, including multiple imputation and complete case analyses, will be performed to evaluate the robustness of results. The secondary outcomes will be analyzed using appropriate mixed or generalized linear models and interpreted as exploratory. Descriptive statistics will summarize categorical variables as frequencies and percentages, and continuous variables as mean (SD), median (IQR), and range.

Predefined subgroup analyses will explore whether treatment effects differ by baseline Hoehn and Yahr stage (≤3.0 vs >3.0), disease duration (<5 vs ≥5 y), age (<65 vs ≥65 y), baseline LEDD (≤ median vs >median), and presence of dyskinesia. Interaction terms will be tested using mixed effects models, and the results will be interpreted as exploratory. Sensitivity analyses will include assessing participants with stable dopaminergic doses (<10% LEDD change) and testing the interaction between treatment allocation and LEDD change to explore medication-dependent effects. Safety analyses will be descriptive, summarizing AEs and serious AEs by treatment group.

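### Adverse events get extra in-patient monitoring in the Ayurveda arm only, so by-group counts of mild events may be inflated there by unequal ascertainment

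*Protocol article*

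**What the plan says.** All references are to the Methods of the protocol article.

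- **Both arms.** Outcome Measures makes a general commitment: "Safety assessments will include monitoring for treatment-emergent adverse events throughout the study period". The Harms section gives the contacts: "Participants will be assessed for AEs at each scheduled follow-up visit (days 60, 120, and 180) and during routine hospital visits".
- **Ayurveda arm only.** Outcome Measures adds: "For participants undergoing Basti therapy, adverse events (AEs) will be monitored during the in-patient care". The Intervention section describes "group A (control group) receiving conventional TAU", and Basti appears only in the group B regimen, once in each of three cycles. No matching extra AE surveillance is described for group A.
- **Setting.** The section on fidelity and adherence begins a sentence: "As panchakarma therapies are delivered in an inpatient or closely supervised setting by trained professionals". It goes on to say that "adherence will be monitored daily through direct supervision and treatment logs". The daily frequency therefore belongs to adherence; none is given for AE monitoring.
- **Analysis.** Statistical Analysis says: "Safety analyses will be descriptive, summarizing AEs and serious AEs by treatment group".
- **Role of safety.** The Hypothesis section expects that the add-on, "when integrated with standard TAU, will be safe and effective in improving clinical and cognitive outcomes".

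**The concern.** Two stated choices fit together poorly: one arm has an additional route by which AEs are found, and the AE summary then sets the arms beside each other. A headache or loose stool on a supervised Basti day is likely to be noted. The same event at home in the control arm is recorded only if it is remembered at a visit up to 60 days later or comes up at a routine visit.

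The by-group summary could then be misread in either direction. With equal true rates, the add-on could appear to cause more mild events than it does. With a real excess, someone could dismiss it as closer observation, and the data as planned might not settle the matter. Safety is half of the trial's stated hypothesis, so readers will compare the two columns even though no test is attached to them.

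**Working it through.** The protocol states no figure for this point, so there is nothing to reproduce. The check measures the extra observation time and then shows what it could do to the counts.

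**Extra supervised time (Group B regimen).** Each cycle has 60 days, with 5 preparatory days and 47 days of oral treatment.

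- Basti days per cycle: 60 − 5 − 47 = 8. This agrees with the number of enemas: 1 + 3 + 3 + 1 = 8.
- Over three cycles: 3 × 8 = 24 of 180 days, or 13.3%. The control arm has none planned.

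**Model.** Assume that the true AE rate is equal in both arms and constant over time, that every event on a supervised day is recorded, and that any other event is recorded with probability p, the same in both arms. With f = 8/60 = 0.1333, the ratio of recorded AEs, Ayurveda to control, is

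ratio = [f + (1 − f) × p] / p.

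| Visit recall p | Recorded share, Ayurveda | Recorded share, control | Ratio |
|---|---|---|---|
| 0.75 | 0.1333 + 0.8667 × 0.75 = 0.783 | 0.75 | 1.04 |
| 0.50 | 0.1333 + 0.8667 × 0.50 = 0.567 | 0.50 | 1.13 |
| 0.25 | 0.1333 + 0.8667 × 0.25 = 0.350 | 0.25 | 1.40 |

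**Sensitivity to detection.** If detection on Basti days is 90% instead of complete, the ratio at p = 0.50 is (0.1333 × 0.9 + 0.8667 × 0.50)/0.50 = 1.11. At p = 0.90 with complete detection it is (0.1333 + 0.8667 × 0.90)/0.90 = 1.01.

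**In participants.** Take 40 per arm and, as a further assumption, one true AE per person per 180 days with Poisson counts. The expected number with at least one recorded AE is 40 × [1 − exp(−recorded share)].

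- p = 0.50: control 40 × [1 − exp(−0.500)] = 15.7; Ayurveda 40 × [1 − exp(−0.567)] = 17.3.
- p = 0.30: recorded share in Ayurveda 0.1333 + 0.8667 × 0.30 = 0.393; control 10.4, Ayurveda 13.0.
- p = 0.70: recorded share in Ayurveda 0.1333 + 0.8667 × 0.70 = 0.740; control 20.1, Ayurveda 20.9.

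The effect is negligible if recall is good and noticeable only if recall over 60 days is poor.

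**The case against.** The strongest case on the other side is that this is an exploratory trial with a purely descriptive safety analysis, so no error rate or power is at stake. Closer observation during a supervised procedure is inherent in comparing an add-on with usual care, and AE table layout is commonly left to an analysis plan that is not shown. The protocol also promises AE monitoring throughout the study for everyone, and telephone contact between visits is not limited to one arm. At good recall the shift is about one participant in 40, well within chance. A comparison confined to shared visits would also remove genuine procedure-related harms and make the add-on look safer than it is.

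Most of this limits the size of the point without removing it. The telephone contacts are described as serving retention and data completeness, not AE collection. Being descriptive does not make the columns comparable. The point rests on the stated monitoring and the stated by-group summary, not on a missing table shell. The warning about a restricted table is right and shapes the fix.

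A reader might infer four stronger things that the text does not support:

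- **That AEs are watched daily during Basti.** Daily monitoring is stated for adherence only. The setting may be in-patient or closely supervised, so the number of in-patient days is not known.
- **That the AE comparison is certain to be distorted.** This depends on recall and detection, for which the protocol gives no figures. A larger ratio, up to 1.65 at 25% recall, needs the 5 preparatory days to be supervised as well (13 of 60 days), which is not stated.
- **That the AE table is the only safety evidence.** Liver, renal and blood count tests are planned with no arm restriction, and each AE is graded for severity, relatedness and expectedness and reviewed by the monitoring board.
- **That the plan fixes a single pooled table.** It says only that AEs are summarised by group.

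**Conclusion.** The point holds as a possible bias and a cheap improvement. The asymmetry is plain in the text: one arm has an AE monitoring route that the other lacks, and the summary is by arm. The likely direction is over-recording of mild, transient events in the Ayurveda arm. The illustrative ratio is 1.04 to 1.40 for visit recall between 75% and 25%, assuming equal and constant true rates and full detection on 8 supervised days per cycle. Recall and detection are assumptions, so the true size could be close to nil. Serious AEs, which are likely to surface whatever the contact schedule, and the scheduled laboratory tests are unlikely to be affected. No type I error, power or efficacy result is touched.

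**What to change.** Leave the monitoring during Basti as it is, and change how AEs are elicited, coded and shown:

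1. Use the same structured AE query in both arms at days 60, 120 and 180.
2. Record for each AE whether it was found during a Basti stay or at a contact both arms share.
3. Present the complete by-group AE table, with all sources and all serious AEs, as the full account.
4. Beside it, present a by-group table restricted to events found at shared contacts, and a separate listing of Basti-stay events.
5. State that the restricted table does not replace the complete one, because events during Basti include real harms of the intervention.

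The cost is one source field per AE and one or two extra tables. Recruitment and follow-up were still under way in August 2025, so the field can be added for remaining participants. For those already followed, the treatment logs should help to show which events fell within a Basti course. The downside is that the restricted table, read alone, could understate procedure-related harms, which is why it must always appear with the complete one.
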